## Abstract

**Background:**

Persons aged ≥ 65 years are currently the world’s fastest growing age group. An important complication of age is the increasing risk of falls. Falls have multifactorial etiology and modifiable risk factors open for interventions in prevention and rehabilitation, are of high interest. In this context, strong hip abductors seem to be important to prevent falls. A newly adapted measurement device to measure hip abductor strength (HAS) in a closed chain position was developed. We aim to assess feasibility, intra- and inter-tester reliability and construct and criterion validity of the new measure.

**Methods:**

In two subsequent parts a feasibility, reliability and validity study with an adapted measurement instrument for the assessment of HAS (index test) in a closed chain position in persons aged ≥ 65 years will be conducted. Part I investigates feasibility of the measure in clinical settings as well as reliability of the new HAS test (*n* = 26). Part II evaluates construct and criterion validity (*n* = 169). Construct validity will be assessed cross-sectional, criterion validity by comparison with prospectively followed up fall history for 12 months (external criterion) and other functional fall risk assessments (Short Physical Performance Battery, Timed Up and Go test, usual gait speed and hand grip strength).

**Discussion:**

Results of feasibility, will give insight in its applicability in daily clinical life and clinimetric properties will show if measurements of HAS in a closed chain position should be encouraged to include in fall risk assessments in older adults.

## Background

Persons aged ≥ 65 years are currently the world’s fastest-growing age group [1]. The United Nations state that one in six persons in the world and one in four persons living in Europe and Northern America will be aged over 65 by 2050 [1]. They also predict that the number of persons over 80 years is going to triple, from 143 million in 2019 to 426 million in 2050 [1].

An important complication of age is the increased risk of falls. About one-third of community dwellings over 65 years and up to half of those in long-term care institutions fall at least once a year [2]. Those impressive numbers show that fall risk detection and prevention is a global public health challenge and should have high priority. Falls can cause serious consequences such as loss of independence [3] and increased mortality [4]. Additionally to a fall itself, older persons are in a high risk to enter in a vicious cycle of deconditioning after a fall [5]. A first fall and related reduced physical conditions combined with fear of falling might lead to insecurity and to even more falls [5]. It is of utmost importance older persons at risk of falls could be detected as soon as possible, to support them in preventing falls and postponing recurrent falls with the aim to reinforce them to reduce serious personal consequences.

Falls have a multifactorial etiology and risk factors can be categorized in environmental, psychological, or cognitive factors, as others linked to medication and physiological aspects [6]. Of high interest are modifiable risk factors open for interventions in prevention and rehabilitation. Compromised mobility, balance as well as diminished strength of the lower extremities are within this context mentioned in a systematic review of Sousa et al.[6].

Functional lower-extremity weakness has been shown important to enhance the risk of the transition from a non-faller into a faller [7]. Hip abductor muscle strength shows a more pronounced decline in older persons than hip extensor muscle strength of the leg [8]. The hip abductor muscle group particularly also is perceived to be important for older persons because of their significant role in maintaining mediolateral balance control [9–11] and their relation to lateral and posterolateral falls [12]. Furthermore, hip frontal plane muscle strength and spinal moments of force are important parameters to counteract destabilization in the mediolateral direction during single-leg support and stabilizing head, arms and trunk over the support leg and thus prevent the center of mass to rapidly fall downward and lateral toward the unsupported swing side [13]. At the actual moment of impact of an acute fall, muscle contraction of the hip abductors also seems to act protectively against stress-induced on the femoral neck and likewise the risk of a femoral fracture [14].

In our previous research about hip abductors strength and fall risk of older persons, we found that hip abductors strength measured in a side-lying position of the participant can discriminate quite well between older fallers and non-fallers [15–17]. However, the hip abductor strength assessment procedure used in these studies was too long (mean 10.58 ± 1.56 min ) for clinical use [16]. A side-lying position also is not functional as falls usually occur during walking and climbing stairs [7]. Measuring hip abductor strength (HAS) in an adapted position; in a standing, closed chain position in which the hip abductors must help stabilize the upper body over the single-leg support and prevent the lateral shift of the center of mass towards the swing side [13], seems much more functional and therefore interesting.

We developed an adapted measurement device, based on our experiences with our already existing measure in a side-lying position, to measure HAS in a closed chain position.

The objective of the present study is to assess feasibility, intra-, and inter-tester reliability as well as construct and criterion validity of the adapted measure in a standing, closed chain position. If reliable and valid this measure would offer caregivers easily feasible possibilities to assess HAS in a functional position in a daily clinical setting. The inclusion of hip abductors strength in the multifactorial assessment of the risk of falls might help to improve the detection of persons at risk of falls and to shape a well targeted guidance for those persons. Benefits will concern a substantial percentage (~ 40 %) [2] of the permanently growing total number of the population aged ≥ 65 years.

## Methods and analysis

A feasibility, reliability, and validity study with a new measurement instrument for the assessment of hip abductor strength (index test) in a closed chain position (described below), in persons aged ≥ 65 years will be conducted in two subsequent parts.

Part I: Feasibility of the measure in clinical settings as well as the intra- and inter-tester reliability of the new hip abductor strength test will be assessed.

Part II: Construct and criterion validity of the hip abductor strength values, assessed with the new measurement instrument, will be evaluated.

The presented study protocol is a clinimetric study nested within a prospective cohort study about an integrative fragility fracture prediction model called AFFIRM-CT study, including participants aged ≥ 65 years. The protocol follows the SPIRIT guidelines, which are an international standard for trial protocols and provide recommendations for their content [18]. Participants flow through the study (part I and part II) is shown in Fig. 1.

**Fig. 1 Fig1:**
[figure not shown]
Flow of participants through the study. PI Principal Investigator, MMSE Mini Mental State Examination, SPPB Short Physical Performance Battery, GS Gait Speed, HAS Hip Abductor Strength, TUG Timed Up and Go, HGS Hand Grip Strength

### The index test; description of the hip abductors strength test used in part I and II

A force measurement device will be attached to the participant with a belt on the height of the great trochanter of the non-tested leg. The participant will be invited to stand sideways close to a wall, with their hip in a neutral position in the sagittal and frontal plane (Fig. 2). The patient’s shoulder should not touch the wall. A chair for stabilization will be placed in front of the tested person.

**Fig. 2 Fig2:**
[figure not shown]
Schematic picture of our measurement instrument and our testing position during the measurement procedure

The participant is invited to raise the non-tested leg (the leg close to the wall) up and flex the knee approximately 20°, in a way that the foot has no floor contact (Fig. 2). The tester stands behind the participant and guides the participant’s pelvis in direction of the wall by tactile and verbal information until the dynamometer is slightly touching the wall (correct starting position).

The participant then is asked to push with the standing leg (the one further away from the wall) as hard (assessment of the maximum voluntary isometric contraction (MVIS)) and in the second round as fast as possible (assessment of the rate of force generation (RFG)) in the direction of the wall to squeeze the dynamometer between the pelvis and the wall. Verbal encouragement will be given by saying to “push”, “push”, “push”, … against the wall over a five second time span. One to three submaximal test trials are used until the participant understands the test movement. The test is repeated three times per leg (6 trials in total for the assessment of MVIS and 6 trials for the RFG of both legs, with a break of 30 s between each trial).

### Part I: Intra- and inter‐tester reliability and feasibility

Reliability, in the context of this study, is « the extent to which scores for patients who have not changed (between the subsequent test performances) are the same for repeated measurements under several conditions: e.g. by different persons on the same occasion (inter-tester); or by the same persons on different occasions (intra-tester)» [19].

#### Study aims and hypotheses

The aims of part I are the evaluation of the intra- and inter-tester reliability of the results of the measurements, by health care professionals. According to our previous studies, we hypothesize that the intra- and inter-tester reliability will achieve ICC_agreement_ values of 0.8 and above, corresponding to good to excellent reliability [20]. We further aim to list some aspects of feasibility of the new testing procedure. We will list if the testing procedure is well tolerated and appreciated by the participants and can be performed in a feasible time frame for clinical use (< 10min).

#### Study design

Part I is a reliability study within a cross-sectional design. It is the first study evaluating the reliability of the new testing procedure and an important first step for a later implementation in daily clinical use.

#### Participants in and exclusion criteria

Participants aged ≥ 65 years, able to walk household distances with or without an assistive device, hospitalized, already participating in the AFFIRM-CT study, and have signed informed consent for this part will be included. We excluded participants with cognitive, orthopedic, or neurological disorders associated with an increased fall risk (e.g. moderate or severe dementia (MMSE < 18) [21], participants with stroke, persons with Parkinson’s disease, persons who had a hip replacement within the previous year) [6, 22] and persons who presented contraindications for or would adversely affect the strength tests (see our previous publication [17]) .

#### Procedure

At the moment of enrollment between January 2021 and January 2023, participants of the cohort of the AFFIRM-CT study will be asked to participate in this nested-in study. The study nurse of the cohort will verbally inform potential study participants about this study and distribute written information. One week after having consented to the study nurse to be approached for the study, the principal investigator (PI) will call the potential study participants to ask if they have questions, if they agree to participate (hand-in the signed informed consent) and give their permission to forward already collected relevant participant information collected within the cohort towards the nested-in study. As soon as the PI obtains the informed consent, the study nurse will consult the participants’ information and check the respective in- and exclusion criteria (described above) for the designated participant. When he can be included, the study nurse will arrange the first appointment. For the diagram of participants flow through the study, the study nurse will record the characteristics of all interested participants in a coded form.

Socio-demographic data (age, sex, height, and weight) will be extracted from the participant record of the cohort study. In addition, participants' fall history in the last 6 months [6] and the Mini Mental State Examination questionnaire (MMSE) [21] will be assessed by the study nurse. Finally, the study nurse will ask the participant to perform the short physical performance battery test (SPPB) [23, 24] and assess her/ his usual gait speed on a 4m walkway [25, 26]. These two functional fall risk assessments are part of the relevant characteristics of the study population.

The inter-tester reliability will be evaluated between two assessors (health care professionals). The exact testing procedure for the index test, hip abductors strength assessment, is described earlier in the method section. For the evaluation of the inter-tester reliability, a concealed allocation of two randomly chosen assessors (health care professionals) will measure the hip abductors strength of a participant with a 5min break between the assessments of the two assessors (see randomization and conceal allocation section below). Similar to instructions in clinical situations, the assessors will get a short 10min instruction of how to use the dynamometer prior to the measurements. The HAS (MVIS and RFG) of the left or right side (randomly chosen) will be evaluated. The patient will be asked to push the dynamometer first as hard as possible (assessment of MVIS) and in a second-round as fast as possible against the wall (assessment of RFG). Every test (MVIS and RFG) will be repeated three times with a break of 30 s between each trial. The two assessors will not discuss the collected strength results and will be blinded to the hip abductors’ strength test results of the other assessor as well as to all fall risk related parameters (e.g. fall history, results of other functional fall risk assessments).

Participants will then have a break of two hours before the re-assessment of their HAS by the pre-designated assessor for the evaluation of the intra-tester reliability.

The intra-tester reliability will be evaluated by two measurements with the same participant and by the same assessor. The two assessments will be done two hours apart, an offset considered to be close enough so that no health status change regarding the HAS measurement is expected but far enough that the participants can recover between the two test sessions. The assessor will be blinded for all fall risk related parameters.

Directly after the two sessions, participants will be asked to answer a short “feasibility” questionnaire about their perception during the test sessions and their respective motivation to complete the tasks. For the assessment of the feasibility of the new measurement instrument, the time to complete the hip abductors strength test will be recorded in seconds for the three trials per leg (one side, MVIS, and RFG). The assessor additionally will be asked to complete a short questionnaire with multiple choice answer options and open questions about the feasibility of the test in clinical life (comprehensibility of the test instructions for the participant and practical points for the installation of the measurement device (belt, manageability of the device, starting and stopping of measurements)). Participants’ also will be asked to complete a questionnaire with closed and open question options about their perception of the test (duration of the test), in case that any pain occurred during or after the test indicate the intensity on the numerating rating scale (NRS) and indicate on a body chart where the pain occurred. Next, there will be some questions about the comprehensibility of the instructions and the test. In both questionnaires, the one for the assessors as well as the one for the participants, a field for comments will allow giving open-ended feedback on all aspects of the measurement feasibility.

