#### Procedure

From January 2021 on, participant recruitment is following the same procedure as described in part I until the scheduling of the first appointment after participants signed the informed consent.

During the first appointment, the study nurse will assess the following fall risk related variables: fall history of the last 6 months [6], poly-medication, and participants’ physical activity level assessed with a physical activity tracker worn on the wrist over 7 days. Then a health care professional blinded for participants’ fall history will assess the following functional fall risk assessments: SPPB [24], TUG [38], usual GS [25], and HGS [40]. Afterward, the second assessor blinded to the test results of the functional fall risk assessments and the fall history of the participants will measure participants’ HAS according to the given description of the index test. This assessor will receive prior to the measurements, a short 10min instruction of the use of the dynamometer, similar, to what would be done in a clinical situation. The HAS of the left and right side will be evaluated either by starting with the randomly chosen right or left side. As described in part I, the MVIS will be measured by asking the participants to push as hard as possible with the dynamometer against the wall (3 times per leg with a break of 30 seconds between each trial). Then the measurements are repeated, this time by pushing the dynamometer as fast as possible against the wall (assessment of the RFG).

Once the hip abductors strength (index test) is evaluated, participants will be followed up for a 12 months period to assess their number of falls (reference test). Participants will be provided with fall diaries in which they are asked to write down their falls and the circumstances/reasons of the falls (intrinsic or extrinsic) and occurring injuries (e.g. fractures) every time such an event will happen. Participants’ will thoroughly be explained what the definition of a fall is and how to fill out the fall diary. A fall is defined as an event resulting in a person inadvertently coming to rest on the ground, floor, or other lower level [2]. Every 6 months, the study nurse will call participants to collect the fall information and provide coaching for the fall diaries if needed.

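### Part I times the strength test on one side only, so that time alone cannot show that the two-leg index test meets the under-10-minute feasibility aim

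*Protocol article*

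**What the plan says.** All references are to the protocol article.

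- **Index test description (stated to serve Parts I and II).** Three repeats per leg, giving "6 trials in total for the assessment of MVIS and 6 trials for the RFG of both legs", so 12 trials. Each push lasts five seconds, trials are separated by 30 s, and one to three submaximal practice trials come first.
- **Part I, Study aims and hypotheses.** The authors will list whether the testing procedure "can be performed in a feasible time frame for clinical use (< 10min"). The section does not say whether this means one leg or both.
- **Part I, Procedure (testing).** "The HAS (MVIS and RFG) of the left or right side (randomly chosen) will be evaluated".
- **Part I, Procedure (timing).** Time is "recorded in seconds for the three trials per leg (one side, MVIS, and RFG").
- **Part I, Randomization and allocation concealment.** One of the two randomizations sets the order of the tested leg, which would suggest that both legs are tested.
- **Part II, Procedure.** "The HAS of the left and right side will be evaluated either by starting with the randomly chosen right or left side".
- **Background.** It says that "the hip abductor strength assessment procedure used in these studies was too long", with a mean of 10.58 ± 1.56 min.

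No section doubles or otherwise rescales the one-side time before it is set against the limit.

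**The concern.** The limit and the measurement refer to different things. The limit applies to the testing procedure, which the article defines as both legs. The clock covers one side. Followed as written, the plan could report that the index test fits the time frame on the basis of half its trials.

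This matters because duration is one of the reasons given for replacing the earlier procedure, and the Discussion says the feasibility data will show whether the device is easy to apply in daily clinical work. A one-leg time does not support that statement for the two-leg test whose validity Part II examines.

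**Working it through.** **Inputs from the index test description:** 3 repeats per leg, 2 modes (MVIS and RFG), 2 legs, 5 s per push, 30 s between trials. **From the Part I aims:** limit under 600 s.

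**1. Trial counts.** Both legs: 3 × 2 legs = 6 per mode, and 6 × 2 modes = 12, which reproduces the protocol's 6 + 6. One side: 3 × 2 modes = 6. The timed share is 6/12 = 50%.

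**2. Minimum push-plus-break time.** For n trials this is n × 5 + (n − 1) × 30 seconds.

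- One side: 6 × 5 + 5 × 30 = 180 s (3.0 min).
- Both legs: 12 × 5 + 11 × 30 = 390 s (6.5 min).
- Timed share: 180/390 = 46%.
- Room left under 10 min for belt fitting, positioning, instruction and practice: 7.0 min on one side, 3.5 min on both.

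**3. One-leg times T that meet the limit while the two-leg test does not.** The protocol gives no set-up time, so take the two extremes. Both assume that turning the participant fits within the 30 s break.

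- No set-up or practice shared between legs: two-leg time = 2T + 30. Setting this to 600 gives T = 285 s (4.75 min).
- All set-up and practice shared: two-leg time = T + (390 − 180) = T + 210. Setting this to 600 gives T = 390 s (6.5 min).

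Below 4.75 min both figures meet the limit. Between 4.75 and 6.5 min the answer depends on how much is shared. From 6.5 min to just under 10 min the one-leg time passes and the two-leg test does not, under either extreme.

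**4. Could one-leg times fall in that range?** The protocol does not say whether practice trials are per leg or per mode. Assume each costs 35 s (5 s push plus 30 s break), with nothing added for belt fitting or turning:

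| Practice trials (assumed) | One side | Both legs |
|---|---|---|
| None | 180 s = 3.0 min | 390 s = 6.5 min |
| 1 per leg | 180 + 35 = 215 s = 3.6 min | 390 + 70 = 460 s = 7.7 min |
| 3 per leg | 180 + 105 = 285 s = 4.75 min | 390 + 210 = 600 s = 10.0 min |
| 3 per leg and mode | 180 + 210 = 390 s = 6.5 min | 390 + 420 = 810 s = 13.5 min |

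The two-leg test may fall on either side of the limit within the practice range that the protocol allows.

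**The case against.** **No decision depends on it.** The aim is to list aspects of feasibility, and the Part I Data analysis section plans descriptive statistics for completion time. There is no pass/fail rule, no gate to Part II, and no effect on the reliability or validity sample sizes. This stands and limits the weight of the point.

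**The time is labelled as one side and could be scaled up.** The labelling is fair. Scaling is only approximate, because the shared set-up is unknown. A one-leg time of 300 s gives between 300 + 210 = 510 s (8.5 min) and 2 × 300 + 30 = 630 s (10.5 min), which straddles the limit.

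**The limit might mean the Part I session.** It sits among the Part I aims, and Part I tests one side. But it is worded for the testing procedure, and the index test description, written for both parts, covers both legs. A sentence restricting the limit to one leg would remove the contradiction, though it would leave the full test untimed. It is also true that no section says clinical use requires both legs.

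**Perhaps both legs are tested in Part I.** The randomization section allows that reading. Even so, the Procedure section describes the timing as one side.

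**Stronger readings to avoid.** A reader might infer that the two-leg test takes longer than 10 min. The documents do not show this, since its minimum is 6.5 min. A reader might also infer that the limit is all but certain to be met on one leg, but no set-up time is given to support that. Nor can the 10.58 min of the earlier procedure be set beside the new time, because the article does not say how many legs it covered. Ranking time as the main feasibility question also goes too far, since tolerance, pain, comprehensibility and device handling are assessed as well.

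**Conclusion.** The point holds as a mismatch between a stated criterion and a stated measurement. Time is recorded on 6 of 12 trials (180 s of the 390 s minimum), and that figure alone cannot establish that the full index test takes under 10 min. The range in which the two answers differ starts between about 4.75 and 6.5 min of one-leg time, depending on shared set-up, and runs to just under 10 min. These bounds rest on the protocol's nominal 5 s pushes and 30 s breaks and on the change of side fitting within one break; a slower change would lower both starting points. Whether the two-leg test in fact meets the limit cannot be known from the documents. The consequence is confined to a descriptive feasibility statement, but the correction is cheap and worth making.

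**What to change.** 1. Add one timing field to the Part II e-CRF for the complete two-leg test, from set-up through practice and change of side to the last trial. Compare that figure with the limit of under 10 min.
2. Report it separately for hospitalized and community-dwelling participants. Part I recruits hospitalized participants only and Part II adds community-dwelling ones, so a pooled Part II time would describe a different population.
3. Label the Part I time as one-leg time and do not present it as evidence that the full test meets the limit.
4. Reconcile the index test description, the Part I Procedure and the Part I randomization section on whether one leg or both are tested in Part I.

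The cost is one e-CRF field and a text correction. Both legs are tested in Part II anyway, so participants do no extra testing. The downside is that the final statement on test time has to wait for the Part II baseline data.
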